## Interim analyses

Analysis of 6-month and 12-month outcomes will be conducted once all 6-month follow-up and 12-month follow-up data has been collected, respectively.

## Missing data

Characteristics of those with missing data (drop outs) and those with complete data as well as group allocation and reason for drop out will be assessed to determine whether data are missing completely at random (MCAR), missing at random (MAR) or missing not at random (MNAR). Depending on the mechanism of missing data (MCAR, MAR, MNAR) an appropriate analytic choice will be made (e.g. completers analysis, multiple imputation or selection models) taking into consideration both bias and preservation of variance.

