# Statistical methods

## Sample size and justification

### Power for primary endpoints

The sample size calculation is based on observing an average weight loss in the intervention group at the end of the intervention (12-months) of 7% of initial body weight[[30](#_ENREF_30)] and allowing for a small regain in weight in the intervention group from 12- to 18-months (+1.2%)[[31](#_ENREF_31)] and small changes in weight among the control group (approx ±1%).[[15-18](#_ENREF_15)] Thus, we expect that weight loss from baseline to 18-months follow-up, expressed as percent of initial body weight, will be at least 5% greater in the intervention group compared to the usual care group**.** Assuming a standard deviation of change of 8.5%[[16](#_ENREF_16)] and allowing 25% attrition at 18-months,[[32](#_ENREF_32)] 80 women per group (160 participants in total) will be needed to detect this minimum difference in weight loss between groups with 90% power and a type I error of 5% (two-tailed).

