## Analytical plan

### 8.3.1 Statistical analyses for primary outcomes

Data analysis will be performed using SAS 9.2. Repeated measures regression model, using linear mixed model will be fitted, for the primary outcome (percent of initial body weight lost), including main effects of group and time and the interaction of group by time. The models will use baseline weight as a covariate to reduce the residual standard error and account for regression to the mean. Potential confounding variables such as stage of disease, menopausal status, treatment and pre-diagnosis weight will be examined to determine whether they are associated with the outcome and if so, will be included as covariates in the model. Statistical significance will be set at p < 0.05 (two-tailed).

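### Section 8.5 makes the primary missing-data method depend on a diagnosis of MCAR, MAR or MNAR that observed data cannot supply, and leaves completers-only as an option

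*Protocol*

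**What the plan says.** Section 8.5 (Missing data) sets a two-step rule. First, the characteristics of women with and without missing data, their allocated group and their reasons for leaving "will be assessed to determine whether data are missing completely at random (MCAR), missing at random (MAR) or missing not at random (MNAR"). Second, the analysis follows from the answer: "Depending on the mechanism of missing data (MCAR, MAR, MNAR) an appropriate analytic choice will be made (e.g. completers analysis", multiple imputation or selection models), with bias and preservation of variance taken into account. No test, threshold, default or blinding of this decision is given.

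Three other places bear on it:

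- Section 8.3.1 names the primary model: "Repeated measures regression model, using linear mixed model will be fitted, for the primary outcome", with group, time, their interaction and baseline weight. It does not say which women or visits enter the model, and does not say that the model holds whatever section 8.5 finds.
- Section 8.3.3 promises sensitivity analyses under differing missing-data assumptions, without naming them.
- Section 4.3 (Withdrawal criteria) says that data gathered before a woman withdraws will be kept and analysed.

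On attrition, section 8.1.1 plans for "allowing 25% attrition at 18-months". No figure is given for 12 months, which the synopsis names as the primary endpoint.

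**The concern.** MAR and MNAR differ only in whether dropout still depends on the unseen weights once the observed data are taken into account. Baseline characteristics, group and stated reasons do not contain those weights, so no comparison of them can settle the matter. MCAR can be rejected by such a comparison but never established. With 25% of 160, about 40 women, a comparison that shows nothing is weak evidence, yet under section 8.5 it would point towards a completers analysis.

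The analysis behind the primary result is therefore open until someone has looked at dropout by group. Completers-only is the option with most to lose: it discards the 6-month weights of women who leave later, which sits badly with the undertaking in section 4.3. Hypothesis 1 in section 3.2 is framed as a difference of at least 5 points at 12 months, so a shift of one or two points could change how the trial reads.

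**Working it through.** **1. The plan's own figure.** Inputs from section 8.1.1: a difference that "will be at least 5% greater in the intervention group compared to the usual care group" (5 points); "Assuming a standard deviation of change of 8.5"%; "with 90% power and a type I error of 5% (two-tailed"); 25% attrition.

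- n per group = 2 × (1.960 + 1.282)² × 8.5² / 5² = 60.7, so 61 evaluable.
- 61 / 0.75 = 81.3, so 82 per group, against the stated 80.
- 80 × 0.75 = 60 evaluable gives 89.7% power.

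The stated size reproduces closely. The point concerns the analysis rule and leaves the sample size alone.

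**2. What observed data can show.**

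| Question | Answerable from dropout comparisons? |
|---|---|
| Is MCAR false? | Yes, if dropout is seen to depend on something observed |
| Is MCAR true? | No; a null result does not establish it |
| MAR or MNAR? | No; this turns on weights that were not recorded |

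Section 8.5 needs all three answers in order to choose a method.

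**3. Size of the completers error.** Within one arm, completer mean − all-randomised mean = dropout share × (completer mean − dropout mean). The error in the treatment difference is this quantity in the intervention arm minus the same quantity in usual care. If the two are equal they cancel; if usual care has the larger one, the effect is understated.

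**4. Simulation.** Only the SD of 8.5 and the 80 per arm come from the protocol. Assumed: true difference 7.0 at 12 months, correlation 0.8 between the 6- and 12-month values, about 26% dropout, and log-odds of dropout rising 0.2 for each point less weight lost at 6 months (0.2 × 8.5 = 1.7 per SD, a strong dependence). This is MAR given the 6-month weight.

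| Dropout pattern | Completers | Estimate using 6-month weights |
|---|---|---|
| Outcome-related in the intervention arm only | about 9.0 | about 7.0 |
| Same slope and same dropout rate in both arms | 7.0 | about 7.0 |
| One common rule: poor losers leave, whichever arm | about 5.8 | about 7.0 |

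By the identity in step 3, the first row's error of 2.0 points implies a 12-month gap of 2.0 / 0.26 = 7.7 points between completers and dropouts in the intervention arm. In the third row usual care loses more women, because they lose less weight, and the error is about −1.2.

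With a slope of 0.05 in the intervention arm only, the error is about 0.7 points (implied gap 0.7 / 0.26 = 2.7 points).

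**5. Would the rule catch it?** If 6-month weight loss is among the characteristics compared, which section 8.5 does not say, the strong one-arm dependence is significant in about 90% of trials pooled over arms and over 99% within the intervention arm. The weak one is found in only 18% to 36%.

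**6. Limit of the mixed model.** If dropout in the intervention arm depends on the final weight itself (MNAR), the estimate using 6-month weights is biased too. With no true difference, a 6-month SD of 6, correlation 0.6 to 0.8, slopes of 0.7 to 1.5 log-odds per SD and 25% dropout, it shows 0.5 to 1.6 points; completers show 1.4 to 2.4.

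**The case against.** The best defence is that section 8.5 does not stand alone. Section 8.3.1 already names a mixed model, multiple imputation can feed that same model, and section 8.3.3 commits to varying the missing-data assumptions. Strong dropout patterns would usually be detected, so completers would not be chosen when they do most harm. All of this stands as mitigation. It does not cure the rule: no default is stated, weaker patterns would often be missed, and sensitivity analyses do not settle which analysis is primary.

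Four stronger readings are tempting, and the protocol does not support them:

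- **That completers analysis would overstate the effect.** This needs outcome-related dropout to be confined to, or stronger in, the intervention arm. Nothing in the protocol says so, and the withdrawal criteria of section 4.3 apply to both arms. The error may be upward, absent or downward.
- **That type I error would be inflated by a known amount.** Always using completers, with one-arm outcome-related dropout under MAR, gave 8.7% to 23.8% when there was no true difference. That is not the behaviour of the section 8.5 selection rule, which was not computed.
- **That sections 8.5 and 8.3.1 contradict each other.** Section 8.3.1 mentions neither all available weights nor MAR, and section 8.5 does not say that it replaces the model. The two are left unconnected.
- **That 25% of women will be missing at the primary time point.** The figure is for 18 months.

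The choice and tuning of an MNAR method is properly left to the SAP, which is not at hand.

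**Conclusion.** The point holds as a fault in a stated rule. Section 8.5 asks for a classification that the data cannot give and ties the primary analysis to it, with completers-only among the options.

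The consequence is a possible bias of either sign: roughly +2 to −1 points under strong dependence on 6-month weight, about 0.7 points under weak one-arm dependence, and none under MCAR or when the two arms' errors cancel. These sizes rest on assumed correlation, slopes, dropout share and, for the common rule, the assumed effect. If 12-month attrition is below 25%, the bias may be smaller. An estimate using the 6-month weights was right in every MAR pattern tried, though not under MNAR.

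This should be fixed before analysis. It does not undermine the design, and the promised sensitivity analyses lessen its weight.

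**What to change.** In section 8.5:

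- Delete the classification step as the basis for choosing the analysis, and report dropout characteristics, group and reasons descriptively.
- Remove completers analysis as a candidate primary analysis.
- State that the section 8.3.1 mixed model, fitted to all randomised women in their allocated group with every available 6-, 12- and 18-month weight (valid under MAR), is primary whatever the dropout comparison shows.

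In section 8.3.3, state that the sensitivity analyses will include at least one departure towards MNAR, for example delta-adjusted imputation, with details left to the SAP.

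The cost is protocol wording and a little programming. No extra participants or data are needed.

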# Study administration and data management

## Protocol deviations

As a general rule, there should be no deviations from study protocol. Should there be a need to deviate from the protocol, this will be discussed with the investigator team and approval sought. The version of this document will be updated with each change/deviation, and each change noted. The revised protocol (including the updated version and protocol number) will then be sent to all reviewing HRECs as an amendment.

## Patient Identification

All patients that return the consent to contact form will be automatically assigned a 3-digit study-specific participant identification number (starting at 100) when their information is entered into the study database. This identification number is used to label all information collected from participants during the course of the study.

## Case Report Forms

Standard data collection forms (identified by participant study number) will be used to record all data collected from participants as part of the study health assessments.

## Data handling

Data collection will occur at the following time points: baseline, 6-months, 12-months, 18-months. All assessment data (body composition assessment, CATI, self-report questionnaire) will be hard-copy recorded using the standard assessment record. Participants’ blood test results will be compiled into a report by SNP and sent to the project manager. Hard-copy assessment data is then entered into the study database. Data will be key-entered twice for verification of correctness and accuracy. Hard copy data collection forms are stored in a locked filing cabinet in the project manager’s locked office. The study database will be stored on a secure network drive and accessible only to authorised project staff members. Results from metabolic and genomic biomarker assays will be provided in an electronic spread sheet.

In addition, data will be collected for participants allocated to the intervention group throughout the 12-month intervention period. The hard-copy data will be kept in a participant case folder by their assigned Lifestyle Coach and entered into the study database. Participant case folders will be handed to the project manager at the completion of the intervention period.

## Record keeping

###

### Patient records

All study records will be stored at the Cancer Prevention Research Centre, The University of Queensland. All data collected as part of study assessments will be kept in paper copy and then entered into the study database. Paper copy records will be stored in a locked filing cabinet in the project manager’s locked office. The study database, which stores all information (identifiable and de-identified) collected throughout the study, is saved in a secure folder on a secure network drive. Access to the study database will only be granted to relevant project staff. Electronic records will be saved in a password protected folder on secure network drive.

All study records will be kept in a secure document storage facility at the University of Queensland for 15 years after the completion of the study, in accordance with The Australian Code for the Responsible Conduct of Research.

### Investigator/site records

As hospitals are only required to disseminate information packs to patients, no records will be held at the hospital sites, all records will be held at the Cancer Prevention Research Centre, The University of Queensland. Some hospital sites may elect to collect signed patient consent to contact forms for the project manager to collect on a weekly basis.

## Training, monitoring and auditing

### Training

Hospital recruitment

As the recruitment protocols have been designed to minimise the time required by hospital recruitment staff (Breast Care Nurses, Cancer Care Coordinators or other nursing staff), no formal training will be required. They will be given a copy of the Hospital Recruitment Procedures document (appendix a), which outlines what the study involves and what their role is, a copy of the patient materials to be disseminated and a script to guide them in discussing the study with their patients.

Assessment and intervention

All project staff undertaking participant assessments will be given an assessment manual outlining assessment protocols, measurement and data entry requirements. Lifestyle Coaches will be given a counsellor manual which outlines the intervention protocols, structure and delivery. In addition, a database manual has been prepared for all staff to follow when entering assessment/intervention data. Telephone interviews (CATI) and intervention counselling calls will be periodically audio-recorded and reviewed by one of the study investigators to ensure adherence to assessment protocols and fidelity of intervention delivery. Regular team meetings will be held to discuss assessment and intervention progress and address any issues that may arise throughout the study.

### Monitoring of recruitment sites

The project manager will contact the primary Breast Cancer Nurse or Cancer Care Coordinator at each hospital once a week (via telephone) to check on recruitment progress, ensure that the study continues to be appropriately introduced and promoted by nurses to potential participants, and to address any issues that may have arisen. Each site will be sent a monthly email to notify them of the number of patients from their hospital that have been recruited into the study (participant names will remain anonymous).

Team meetings will be held fortnightly with the investigator team and project staff to report on recruitment progress, both at the hospitals (consent to contact) and on-site (consent to participate).

### Audits

All data collected (body composition assessment, telephone interviews, self-report questionnaire, blood test results) will be key-entered twice for verification of correctness and accuracy. In addition, telephone interviews and intervention calls will periodically be audio-recorded and reviewed by one of the investigators to check for adherence to assessment/intervention protocols.

## Cost assessment

This study has been fully costed with all elements (e.g., project staff salaries, equipment, recruitment, assessment and intervention calls and materials) covered by the NHRMC Project Grant funding and in-kind support from Cancer Prevention Research Centre.

# Regulatory considerations

## Participant consent

The nature of the study, what participation will involve, benefits and known risks of participation will be explained to the patients in a written document (Participant Information Sheet) (appendix d) and verbally (Screening and Recruitment call). The Participant Information Sheet will address the participant’s right to informed consent and the obligations of the researchers under privacy legislation in concordance with individual institutional ethics committees.

Written informed consent will be gained from each participant **prior** to commencing participation in the study (appendix e). Consent will be documented in the study database (accessible only to authorised persons) and the paper copy will be stored securely in a locked filing cabinet in the project manager’s locked office where it will be available for future reference.

## Compliance with regulatory guidelines

This study will be conducted in compliance with:

- the National Health and Medical Research Council National Statement on Ethical Conduct in Human Research (2007)
- The Australian Code for the Responsible Conduct of Research (2007)

## Ethical review

The study proposal received ethical approval from the Greenslopes Private Hospital HREC to cover recruitment at Greenslopes Private Hospital and North West Private Hospital on 19/06/2012. Royal Brisbane and Women’s Hospital HREC approval was received on 17/08/2012 to cover the Royal Brisbane and Women’s Hospital, Redcliffe Hospital, Mater Public Hospital and Mater Private Hospital. Ethical approval was granted from the University of Queensland Medical Research Ethics Committee on 22/08/2012. St Vincent’s Health & Aged Care HREC approval was received on 18/06/2013 to cover Holy Spirit Northside Private Hospital.

An amendment to the study protocol and recruitment documents was submitted to Greenslopes Private Hospital HREC based on RBWH HREC feedback (approved 12/08/2012).

Approval will be gained from the Director-General of Queensland Health to cover recruitment of breast cancer patients through the Queensland Cancer Registry (via electronic pathology reports).

Metro North Hospital and Health Service Research Governance approval was received on 13/09/2012 to cover the study recruitment at Redcliffe Hospital and on 14/11/2012 to cover the study recruitment at Royal Brisbane and Women’s Hospital. Mater Health Services Research Governance approval was granted on 27/11/2012 to cover study recruitment at Mater Adult Hospital and Mater Private Hospital.

During the course of the study, the chief investigator is required to submit to the HRECs the following:

- amendments to the protocol,
- serious and unexpected adverse events and the outcome,
- specific site updates as agreed to by the investigator and respective HREC, and
- any additional information (e.g., unexpected serious adverse events reported by other sites, administrative changes to the protocol).

At the end of the study, the Investigator is required to inform the HREC in writing that the study has ended and no further activities regarding this protocol will be conducted at the site.

# List of Appendices

Appendix a) Hospital Recruitment Procedures

Appendix b) Patient Information Brochure

Appendix c) Consent to Contact Form

Appendix d) Participant Information Sheet

Appendix e) Participant Consent Form

Appendix f) Recruitment Screening Script

Appendix g) Body Composition Assessment Form

Appendix h) Telephone Interview Script

Appendix i) Self-report Questionnaire

Appendix j) Participant Satisfaction Survey

Appendix k) Adverse Event Report Form
